### Outcomes

In this study, the primary outcome will be the distribution of scores on the NIHSS before and after treatment among patients. Secondary outcomes will be assessed at different follow-up visits and will include death, a composite of new clinical vascular events, neurological function, and improvement of traditional Chinese medicine syndrome. Safety assessment will be performed by monitoring adverse events. The complete study outcomes are illustrated in Table 2.

**Table 2 table2:** Outcome variables and definitions.

Outcome variables		Definitions
**Primary outcome**		
	Improvement degree of clinical NIHSS^a^ scores	Basic recovery (NIHSS score decreased by more than 90%) Significant improvement (NIHSS score decreased by 46%-89%) Improvement (NIHSS score decreased by 18%-45%) No change (NIHSS score decreased 0%-18% or increased<18%) Deterioration (NIHSS score increased more than 18%) The basic recovery, significant improvement, and improvement were regarded as effective. The no change, deterioration, and death were regarded as inefficient [19]
**Secondary outcomes**		
	Overall mortality	—^b^
	Stroke recurrence	—
	New-onset major vascular events	Major adverse vascular events include ischemic stroke, hemorrhagic stroke, transient ischemic attack, myocardial infarction, and vascular-related death
	Global disability	Measured by BI^c^ and mRS^d^ scale
	improvement of TCM^e^ syndrome	Measured by TCM questionnaire
	Adverse events	Undesirable experiences occurring to participants during the trial are considered to be related to the DJHJTIf

^a^NIHSS: National Institute of Health Stroke Scale.

^b^Not available.

^c^BI: Barthel Index.

^d^mRS: modified Rankin Scale.

^e^TCM: traditional Chinese medicine.

^f^DZHJTI: Dazhu hongjingtian injection.

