**Objective:**

The primary aim of this study is to evaluate the effectiveness of DZHJTI treatment for AIS with regard to changes in the stroke-related neurological deficit from baseline to outpatient follow-up, mortality, subsequent vascular events, disability, and traditional Chinese medicine syndrome in real-world clinical settings. By monitoring for adverse events or significant changes in vital signs and laboratory parameters, we also aim to assess the safety of DZHJTI.

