**Methods:**

This prospective, multicenter cohort study plans to enroll 2000 patients with AIS within 14 days of symptom onset from 30 hospitals across China. Eligible patients will be followed up for 6 months after initiating medication treatments. The primary outcome will be the change in the National Institute of Health Stroke Scale score from baseline to outpatient follow-up. The secondary outcomes include overall mortality, stroke recurrence, new-onset major vascular events, global disability, and improvement of traditional Chinese medicine syndrome in 6 months. Adverse events or clinically significant changes in vital signs and laboratory parameters, regardless of the severity, will be recorded during the trial to assess the safety of DZHJTI. An augmented inverse propensity weighted estimator will be used to reduce variability and improve accuracy in average treatment effects estimation.

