## Methods

### Study Design

Our study is a prospective, multicenter cohort study conducted in a real-world setting. An overview of the study flowchart is presented in Figure 2. It is planned to enroll 2000 patients with AIS, as defined in the *Chinese Guidelines for Diagnosis and Treatment of Acute Ischemic Stroke 2018* [15] and *Stroke Diagnosis and Effectiveness Evaluation Standards* [16]. A total of 3 visits will be carried out within a 6-month follow-up period. Baseline demographic data, therapeutic effects, adverse events, and complications associated with DZHJTI will be analyzed.

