### Treatment Regimens

All patients will receive current guideline-recommended treatments according to *Chinese Guidelines for the Diagnosis and Treatment of Acute Ischemic Stroke 2018* [15]. The most commonly used medications and treatments include intravenous thrombolysis drugs, antiplatelets, anticoagulants, drugs for volume expansion, neuroprotectants, medicines for improving cerebral blood flow, and traditional Chinese medicine. Cases will be recruited from patients who receive DZHJTI according to the physician’s order. The DZHJTI will be manufactured and supplied by Tonghua Yusheng Pharmaceutical Co, Ltd (approvals Z20060361 and Z20060362), with identical appearance, color, and flavor. The fingerprint-based quality control and ingredient identification met the Chinese pharmacopeia’s reference requirements (detailed information is provided in Multimedia Appendix 1). The administration and dosage of DZHJTI will be determined by the attending physicians based on the patients’ medical history and clinical manifestations.

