### Data Collection and Monitoring

Trained research personnel at each participating site will collect baseline data during patient admission, including prehospital care and treatment, prestroke symptoms, and the NIHSS. They will also conduct assessments using the prestroke modified Rankin Scale scores and Barthel Index. Patient information, including demographics, medical and family history, physical examination, auxiliary examination, risk factor assessment, and clinical diagnosis, will be obtained from medical records. The classification of stroke etiology, related complications, and new cerebrovascular events will be documented, and the etiology of AIS will be determined according to the Trial of Org 10172 in Acute Stroke Treatment criteria [17]. Besides standard therapies, the administration of DJHJTI during hospitalization will be documented by the research team.

The collection and reporting of data will use a secure electronic data capture (EDC) system that follows the current clinical protocol and provides each patient with a unique ID. Authorized research personnel can access the EDC system both on personal computers and smartphones, enabling them to complete data collection during daily ward rounds. An overview of the measurement data collection schedule is shown in Table 1. In the EDC system, personal identifiers such as names, ID numbers, and contact information are removed or replaced with unique codes to ensure participant anonymity.

**Table 1 table1:** Schedule of assessments in the cohort study.

Participant assessment	Time point and form				
	Baseline (acute phase)		Follow-up 1	Follow-up 2	Follow-up 3
	Admission	Discharge	1 month	3 months	6 months
	Visit	Visit	Visit or telephone interview	Visit or telephone interview	Visit or telephone interview
Eligibility screen	✓^a^				
Informed consent	✓				
Demographic and anthropometric data	✓				
TCM^b^ questionnaire	✓				
NIHSS^c^	✓	✓			
mRS^d^	✓	✓	✓	✓	✓
BI^e^			✓	✓	✓
Laboratory examination	✓	✓	+^f^	+	+
Imaging examination	✓	✓	+	+	+
Admission status		✓			
Discharge status		✓			
Follow-up interview			✓	✓	✓
AE^g^		+	+	+	+
Outcomes		+	+	+	+

^a^Required data.

^b^TCM: traditional Chinese medicine.

^c^NIHSS: National Institutes of Health Stroke Scale.

^d^mRS: modified Rankin Scale.

^e^BI: Barthel Index.

^f^Optional data to be collected based on the actual occurrence of related events in patients.

^g^AE: adverse events.

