### Sample Size

According to the previous studies, the ineffective rate assessed by NIHSS score (percentage of patients experiencing no change and deterioration) in controls was 8.75% (7/80), and the ratio of cases to controls was 0.31 [14]. To test the hypothesis that adjuvant treatment with DZHJTI significantly reduces the ineffective rate with a 2-sided α of .05, power of 0.80, and a 20% (n=248) dropout rate, a sample size of 619 cases in each group is required. Nevertheless, a sufficiently large sample size is also necessary to reduce the bias in real-world studies. Therefore, a total of 1000 case participants per group will be included.

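### Table 2 defines adverse events by their relation to DZHJTI, so this outcome cannot be validly compared between the treated and control groups

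*Protocol article*

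**What the plan says.** The Outcomes section of the protocol article refers the reader to Table 2 for the complete list of outcomes. Among the secondary outcomes there, adverse events are defined as follows: "Undesirable experiences occurring to participants during the trial are considered to be related to the" injection (its abbreviation is misprinted in that cell, which does not matter here). No other operational definition of an adverse event appears in the article.

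The other safety statements carry no such condition:

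- Objective: "By monitoring for adverse events or significant changes in vital signs and laboratory parameters, we also aim to assess the safety of DZHJTI".
- Abstract, Methods: "Adverse events or clinically significant changes in vital signs and laboratory parameters, regardless of the severity, will be recorded during the trial".
- Outcomes, running text: "Safety assessment will be performed by monitoring adverse events".

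The Study Design section is closer to Table 2: "adverse events, and complications associated with DZHJTI will be analyzed".

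On exposure, Treatment Regimens states that "Cases will be recruited from patients who receive DZHJTI" on the physician's order. The exclusion criteria remove controls who used other dosage forms. On size, the Sample Size section says that "a total of 1000 case participants per group will be included".

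**The concern.** Safety is a stated aim, and the study has a concurrent control group. The useful safety question is whether adding DZHJTI to guideline care raises the frequency of untoward events. Answering it needs an event definition that applies equally to both groups. A definition that builds in attribution to one group's treatment turns the outcome into a causality judgement, which can only be made for exposed patients.

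These patients have an acute stroke and, according to Treatment Regimens, may receive thrombolysis, antiplatelets, anticoagulants and other drugs. Background events are therefore to be expected in both groups, and the control group is what allows them to be separated from harm due to the injection. If sites follow Table 2, that background may not be recorded in controls. The weighted estimator in the Statistical Analysis section cannot restore events that were never collected.

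**Working it through.** The plan gives no figure to reproduce, because this point concerns a definition. The check is to apply the definition to each group under each reading and then to see what a comparison would show.

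**Inputs from the article.** Two groups, 1000 planned in each (Sample Size). The exposed group receives DZHJTI and controls do not (Treatment Regimens, exclusion criteria). Two-sided significance level 0.05 (Statistical Analysis).

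**Reading 1: only experiences judged related to DZHJTI count.** Let *a* be the all-cause event risk, equal in both groups, and *r* the share of events in the exposed group that are judged related.

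- Exposed group: expected risk *a* × *r*.
- Control group: 0, because no event can be related to a drug not received. The planned count is 0 of 1000.
- Apparent difference: *a* × *r* − 0 = *a* × *r*, which is above zero whenever any event is attributed, although the true difference is *a* − *a* = 0.
- Risk ratio: (*a* × *r*) / 0, undefined.

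To show how readily this would look like a signal, take *k* attributed events in the exposed group and 0 in controls, with 1000 per group. The two-sided Fisher exact p-value is 2 × C(1000, *k*) / C(2000, *k*). The values of *k* are assumptions, since the article gives no adverse-event rate.

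| Attributed events, DZHJTI | Controls | p |
|---|---|---|
| 5 | 0 | 0.062 |
| 6 | 0 | 0.031 |
| 10 | 0 | 0.0019 |
| 20 | 0 | 1.7 × 10⁻⁶ |

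For *k* = 5: 2 × (1000/2000) × (999/1999) × (998/1998) × (997/1997) × (996/1996) = 0.062. Multiplying by 995/1995 gives 0.031 for *k* = 6. Six attributed events in 1000 (0.6%) would cross the 0.05 level even with equal all-cause rates.

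**Reading 2: every undesirable experience is deemed related.** In the exposed group, *r* = 1, so the whole of *a*, including stroke complications and effects of other drugs, is charged to DZHJTI. In controls, the definition calls events related to a drug those patients did not receive, which has no meaning. The counts could be compared only by ignoring the relatedness clause, that is, by using a different definition from the one written.

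**Against the other safety text.** The Objective, the Abstract and the running Outcomes text set no relatedness condition. The Abstract's qualifier concerns severity, not causality, so it neither repeats nor repairs the condition in Table 2. The passages need to be reconciled.

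**The case against.** The strongest reply is that Table 2 holds one badly worded sentence, that the rest of the article describes broad safety monitoring, and that sites may already record all events in both groups. That may be so, and correcting Table 2 would then cost one sentence. But Table 2 is where the article sends the reader for the outcomes, and it holds the only definition, so the wording has to be right.

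It can also be said that no between-group test of adverse events is expressly promised. This is fair: the Statistical Analysis section mentions between-group comparisons only in general, and a description of reactions in exposed patients would meet a limited form of the aim. Such a description would not use the control group.

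Several stronger readings are tempting, and the article does not support them.

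- *No comparative safety result of any kind is possible.* Mortality, stroke recurrence and major vascular events, including hemorrhagic stroke and myocardial infarction, carry no relatedness condition. Laboratory tests are required at admission and discharge without a split by group. All of these can be compared.
- *The control count is zero by definition.* This holds under reading 1 only.
- *Laboratory testing after discharge differs between groups.* The Table 1 footnote says "Optional data to be collected based on the actual occurrence of related events in patients". It does not mention DZHJTI or the groups, and the word about relation may mean only that the event is relevant to the test.
- *Vital signs are not collected, because Table 1 has no such row.* A condensed article commonly leaves such detail to the full protocol, and the Objective and Abstract commit to monitoring them.
- *Relatedness is judged by unblinded assessors.* The article does not say who judges it or what they know. In an observational cohort this is plausible, but it is inference.

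**Conclusion.** The point holds for the outcome labelled adverse events, and no further. As defined in Table 2, that outcome permits no valid between-group result under either reading, and the definition conflicts with the broader monitoring described in the Objective, the Abstract and the Outcomes text.

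The size depends on the reading. Under reading 1 the bias in the risk difference is the whole attributed rate in the DZHJTI group and the risk ratio is undefined. Under reading 2 the error is the misattribution of all background events to DZHJTI. The article supplies no event rate, so the p-values above illustrate the mechanism and do not forecast a result. They assume 1000 evaluable patients per group and an unweighted comparison.

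Deaths and vascular events do not fill the gap, because they miss non-vascular harms such as allergic reactions, and allergy is among the contraindications the article lists.

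**What to change.** Reword the adverse-event line of Table 2 as any untoward medical event, including a clinically significant change in vital signs or laboratory values, that occurs in either group during follow-up, regardless of causality. Record relatedness to DZHJTI as a separate attribute of each event in exposed patients. Base the between-group safety comparison on all-cause adverse events, and present events judged related as a description of the DZHJTI group. Align the Study Design sentence and the instructions to sites with this definition.

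The cost is a change of wording and somewhat more adverse-event recording in controls; sample size and treatment are unaffected. Recruitment began in November 2022, so if sites have been applying Table 2 as written, events in controls already enrolled may be incompletely captured. The date of the change and this limitation should be stated when the results are reported.

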### Study Sites and Data Source

The cohort study’s steering committee will conduct a rigorous screening process of hospitals nationwide, aiming to represent the population from each region in mainland China. Only hospitals admitting over 100 patients with stroke annually, experienced in multicenter studies, and equipped with magnetic resonance imaging or computed tomography machines will be considered. After a thorough evaluation, 30 participating sites with proven research capabilities and a demonstrated commitment to the study will be selected.

### Quality Control and Management

Before the study begins, the steering committee will create training materials outlining the study protocol and standard operating procedures for patient screening, recruitment, informed consent, and data collection. Research personnel must complete the training videos and pass an examination to obtain a study permit. The end-point judgment committee will establish standard operating procedures for the proper use of scales, outcome assessment, and reporting procedures. An independent data safety and monitoring board will oversee data monitoring to guarantee adherence to the study documentation, reporting procedures, and the study protocol. This board will be responsible for ensuring that the study is conducted in accordance with good clinical practice guidelines.

### Sample Size

According to the previous studies, the ineffective rate assessed by NIHSS score (percentage of patients experiencing no change and deterioration) in controls was 8.75% (7/80), and the ratio of cases to controls was 0.31 [14]. To test the hypothesis that adjuvant treatment with DZHJTI significantly reduces the ineffective rate with a 2-sided α of .05, power of 0.80, and a 20% (n=248) dropout rate, a sample size of 619 cases in each group is required. Nevertheless, a sufficiently large sample size is also necessary to reduce the bias in real-world studies. Therefore, a total of 1000 case participants per group will be included.

### Statistical Analysis

A statistical analysis plan was developed prior to initiating the cohort study. Continuous data will be summarized using mean, median, standard deviation, or IQR, while categorical data will be presented as counts and percentages. Between-group comparisons will be conducted using appropriate parametric tests (such as the 2-tailed Student *t* test) or nonparametric tests (such as the chi-square test, Fisher exact test, or Mann-Whitney *U* test). Time-to-event analysis will involve censoring patients at their last follow-up assessment when experiencing a clinical event, at the end of the study, or at the time of withdrawal from the study. Cumulative clinical events will be reported as Kaplan-Meier estimates. Hazard ratios will be calculated at 95% CIs using Cox proportional hazard regression methods.

During data analysis, both confounding factors and missing values will be taken into account. The augmented inverse propensity weighted (AIPW) estimator will be used to obtain a marginal estimate of the treatment effect rather than a conditional estimate. AIPW analysis creates a pseudopopulation in which the relationship between the confounders and the exposure is blocked. Multiple imputation will be used to handle missing values of covariates, and both complete case and imputed data sets will be analyzed. For each imputed data set, the AIPW estimator will be used to estimate the treatment effect, and Rubin rules will be used to combine these estimates and obtain an overall estimate [20]. Sensitivity analyses for unmeasured confounding in observational studies will be performed using the methodology proposed by VanderWeele and Ding [21]. All statistical tests will be 2-sided with statistical significance set at *P*<.05. Statistical analyses will be conducted using SAS software (version 9.4; SAS Institute Inc).

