### Follow-Up Procedures

All patients will be identified and followed up using individual identity cards, which are mandatory for all Chinese citizens, enabling unambiguous linkages. Research personnel will conduct regular face-to-face or telephone follow-up at 1, 3, and 6 months after stroke onset. Information on patient outcomes, including mortality, functional status, activities of daily living, cognitive function, and cardiovascular or cerebrovascular events, will be obtained during follow-up. Mortality will be confirmed through a death certificate issued by the local civil registry or the attending hospital. New cardiovascular or cerebrovascular events requiring rehospitalization will be verified by the discharge diagnosis. In the absence of hospitalization, a committee responsible for determining end points will evaluate suspected recurrent cardiovascular or cerebrovascular events [18].

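### The censoring rule treats a clinical event as a reason for censoring, which contradicts the Kaplan-Meier and Cox analyses of those same events (secondary outcomes only)

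*Protocol article*

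**What the plan says.** The rule in the protocol article, Statistical Analysis, reads: "Time-to-event analysis will involve censoring patients at their last follow-up assessment when experiencing a clinical event", and then adds study end and withdrawal as the second and third occasions. The two sentences that follow name the analyses it governs: "Cumulative clinical events will be reported as Kaplan-Meier estimates" and "Hazard ratios will be calculated at 95% CIs using Cox proportional hazard regression methods".

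The events in question are study outcomes. The Outcomes section states: "Secondary outcomes will be assessed at different follow-up visits and will include death, a composite of new clinical vascular events". Table 2 lists overall mortality, stroke recurrence and new-onset major vascular events as secondary outcomes, and defines the last of these: "Major adverse vascular events include ischemic stroke, hemorrhagic stroke, transient ischemic attack, myocardial infarction, and vascular-related death".

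The assessment times are in Follow-Up Procedures: "Research personnel will conduct regular face-to-face or telephone follow-up at 1, 3, and 6 months after stroke onset". Table 1 adds an assessment at discharge.

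**The concern.** In a time-to-event analysis a patient either has the event, and contributes a failure at its date, or does not, and is censored when observation stops. The stated rule puts the event itself on the censoring side. The same term, clinical event, then names what the Kaplan-Meier analysis is to accumulate, so the plan removes what it sets out to count.

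The dating has its own problem. The rule ties the time to the last follow-up assessment, and the assessments after discharge are one to three months apart. Even an analyst who codes the event as a failure is told to use a visit date.

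At stake are the estimates for death, stroke recurrence and major vascular events. These are secondary outcomes, but mortality and subsequent vascular events also appear in the study objective in the Abstract. If the published rule cannot be carried out as written, the event coding has to be settled later, possibly with data in hand.

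**Working it through.** The article gives no event rate, event count or hazard ratio for these outcomes, so there is no figure of the plan's to reproduce. The check applies the rule as written and then in its most charitable form.

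**Inputs from the article**
- Occasions for censoring: clinical event, end of study, withdrawal (Statistical Analysis).
- Quantities to be reported: Kaplan-Meier cumulative clinical events and Cox hazard ratios (Statistical Analysis).
- Visits at 1, 3 and 6 months (Follow-Up Procedures).
- Planned size (Sample Size): "Therefore, a total of 1000 case participants per group will be included".

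**Assumed, for illustration only:** true 6-month risks of 5%, 10% and 15%, a constant hazard, and no loss to follow-up.

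**Step 1. Literal reading.** The Kaplan-Meier estimate is S(t) = product over event times of (1 − d_j/n_j), where d_j is the number of failures and n_j the number at risk. If every patient with an event is coded as censored, d_j = 0 throughout, so S(t) = 1 and cumulative incidence is 0%. The Cox partial likelihood has one factor per failure. With no failures it has no factors, so no hazard ratio exists.

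| Assumed 6-month risk | Expected events per group of 1000 | Events counted under the literal rule |
|---|---|---|
| 5% | 1000 × 0.05 = 50 | 0 |
| 10% | 1000 × 0.10 = 100 | 0 |
| 15% | 1000 × 0.15 = 150 | 0 |

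The right-hand column does not depend on the assumed risk.

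**Step 2. Charitable reading.** Suppose the event is a failure and only its date follows the sentence. If the last follow-up assessment means the visit before the event, an event in month 5 is dated at month 3. The largest shift equals the gap between visits: 3 − 1 = 2 months in the second interval and 6 − 3 = 3 months in the third. If it means the visit at which the event is reported, the shift runs the other way and has the same maximum.

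The effect on the curve can be seen at 3 months under preceding-visit dating. With a constant hazard the true 3-month risk is 1 − √(1 − 6-month risk). All events from months 3 to 6 are pulled back to month 3, so the curve there already shows the full 6-month risk.

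| Assumed 6-month risk | True 3-month risk | 3-month value with preceding-visit dating |
|---|---|---|
| 5% | 1 − √0.95 = 2.5% | 5% |
| 10% | 1 − √0.90 = 5.1% | 10% |
| 15% | 1 − √0.85 = 7.8% | 15% |

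With complete follow-up the 6-month value itself does not change. The order of events across visit intervals is kept and the same rule applies to both groups, so a hazard ratio should suffer less than the curve, mainly through ties.

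**Step 3. Does another section repair the rule?** Follow-Up Procedures describes how deaths and new vascular events are confirmed, by death certificate, discharge diagnosis or an end-point committee. It does not say how they enter the analysis. Outcomes and Table 2 give definitions only. Nothing in the article says that an event is a failure at its own date, or limits the censoring rule to events other than the outcome being analysed.

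**The case against.** The best defence is that nobody would run the rule literally. The next sentence requires cumulative events to be reported, so an analyst who coded them all as censored would see an empty result at the first run. The likely intent is that follow-up ends at the first of event, study end or withdrawal, with only event-free patients censored. A separate statistical analysis plan is said to exist and may state this correctly. The primary outcome and the sample size rest on NIHSS response, which the sentence does not touch.

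Most of this stands, and it limits the severity. It does not remove the point. The article is not silent here: it states a rule, and the rule is wrong as written. The dating problem also survives the charitable reading and, unlike an empty result, would not announce itself.

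A reader might infer two stronger things that the article does not support.

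- *That a non-fatal stroke or infarction takes a patient out of the mortality analysis, so that mortality is understated through informative censoring.* The text nowhere says that an event of one type censors follow-up for another. Any size put on such a bias would come from assumed inputs alone.
- *That the Kaplan-Meier curves and hazard ratios are unadjusted and therefore confounded.* This would be an inference from silence. The section specifies Cox regression. Its next paragraph says, without restriction to any outcome, that confounding will be handled in the analysis, and it plans AIPW estimation and a sensitivity analysis for unmeasured confounding. Covariates and weighting are details that an article may leave to the analysis plan.

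**Conclusion.** The point holds as a contradiction within one section. The censoring rule lists the clinical event as a reason for censoring, while the sentences after it make clinical events the subject of Kaplan-Meier and Cox analyses. The literal consequence (zero failures, 0% incidence, no hazard ratio) follows from the wording and needs no assumption. The consequence under the charitable reading, a date wrong by up to about 3 months, follows from the visit schedule. The 3-month percentages shown are illustrations that rest on assumed risks, a constant hazard and complete follow-up.

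The reach is limited to mortality, stroke recurrence and major vascular events. The primary NIHSS outcome is unaffected, and the sentence is probably a drafting slip. It should be corrected before the analysis, but it does not put the study's main conclusion at risk.

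**What to change.** Replace the sentence in Statistical Analysis with: *For each time-to-event outcome, the first occurrence is the event, dated at its onset; patients without that event are censored at last contact, withdrawal or 6 months, whichever is first; a non-fatal event does not end follow-up for death.* The last clause is there because overall mortality is a separate outcome, and it closes off the cross-censoring reading.

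Check that the statistical analysis plan carries the same rule, and that the data capture form records an onset date for each event as well as the visit at which it was reported. The death certificates and discharge diagnoses already used to confirm events should supply most of these dates.

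Handling death as a competing event for non-fatal outcomes, and weighting the curves, are options for the analysis plan and not part of this correction. The cost is a wording change and minor programming, with no new patients, visits or outcome data.

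### Mortality is censored at study withdrawal, although the article says every patient is followed by identity card, so deaths after withdrawal can go uncounted

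*Protocol article*

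**What the plan says.** **Censoring (Statistical Analysis).** A single sentence covers all time-to-event outcomes. It begins "Time-to-event analysis will involve censoring patients at their last follow-up assessment when experiencing a clinical event, at the end of the study, or at the", and its last two censoring points read in full "at the end of the study, or at the time of withdrawal from the study". Kaplan-Meier estimates and Cox hazard ratios follow. The section does not list which outcomes are analysed this way. Overall mortality is the natural one, and no separate rule is given for it.

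**Follow-up (Follow-Up Procedures).** "All patients will be identified and followed up using individual identity cards, which are mandatory for all Chinese citizens, enabling unambiguous linkages." The next sentence gives the contact schedule: "Research personnel will conduct regular face-to-face or telephone follow-up at 1, 3, and 6 months after stroke onset." Mortality is among the information gathered at these contacts. On the source document for death: "Mortality will be confirmed through a death certificate issued by the local civil registry or the attending hospital."

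**Role of mortality (Abstract; Table 2).** "The secondary outcomes include overall mortality, stroke recurrence, new-onset major vascular events, global disability, and improvement of traditional Chinese medicine syndrome in 6 months." Vascular-related death is also a component of the major vascular event outcome in Table 2.

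**Dropout (Sample Size).** The calculation uses "power of 0.80, and a 20% (n=248) dropout rate". It concerns the ineffective rate on the NIHSS.

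**The concern.** Withdrawal from visits or calls ends a patient's willingness to be assessed. It does not by itself end the possibility of knowing whether the patient is alive. The follow-up section describes patient identification that does not depend on continued contact and names registry and hospital certificates as evidence of death. The censoring rule nevertheless closes the mortality record on the day of withdrawal.

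Kaplan-Meier and Cox methods need censoring that is unrelated to the risk of death. Table 1 allows all three follow-ups by telephone. Textbox 1 excludes NIHSS 0-5, so decline is a plausible reason for leaving. Treatment follows the physician's order and no blinding is described, so withdrawal could also differ between groups. If it does, the hazard ratio can be distorted in either direction.

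The remedies named in the article do not address this. Multiple imputation is for covariates, and the stated sensitivity analysis concerns unmeasured confounding.

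**Working it through.** **1. The two sections side by side.**

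| Question | Follow-Up Procedures | Statistical Analysis |
|---|---|---|
| Who is followed? | All patients, by identity card | Patients up to withdrawal |
| What establishes a death? | Registry or hospital certificate | Not stated |
| Does a death after withdrawal count? | Could be known through the stated means | No, the patient is already censored |

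If the identity-card route is used after withdrawal, the censoring rule discards what it finds. If it is not used, follow-up of all patients is not delivered for those who withdraw. Either way the sections need reconciling.

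**2. The plan's own dropout figure.** 0.20 × 2 × 619 = 247.6, which rounds to the stated 248. The 20% is therefore consistent with its count, but it is a sample-size allowance for the NIHSS outcome. Below it serves only as an illustrative withdrawal proportion: 0.20 × 2000 = 400 patients.

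**3. Deaths left out if withdrawal is unrelated to prognosis.** The article gives no mortality rate, so 6-month mortality m is an assumption. With a constant hazard, h = −ln(1 − m)/6 per month. If 400 patients withdraw evenly over 6 months, the expected deaths after withdrawal are 400 × [m/(6h) − (1 − m)].

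| Assumed m | Deaths after withdrawal | All deaths in 2000 |
|---|---|---|
| 3% | about 6 | 60 |
| 5% | about 10 | 100 |
| 10% | about 20 | 200 |
| 15% | about 29 | 300 |

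These deaths are uncounted, but in this case the Kaplan-Meier estimate is not biased.

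**4. Bias if withdrawal is related to prognosis.** Assume that 20% leave at 1 month and then have k times the hazard of those who stay.

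- Kaplan-Meier survival at 6 months: exp(−h) × exp(−5h) = 1 − m
- True survival: exp(−h) × [0.8 exp(−5h) + 0.2 exp(−5kh)]

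For m = 5%, h = 0.05129/6 = 0.00855. With k = 2, true survival is 0.9915 × (0.8 × 0.9582 + 0.2 × 0.9181) = 0.9420, so true mortality is 5.80% against an estimate of 5.00%.

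| m (Kaplan-Meier estimate) | k | True mortality | Understatement (points) |
|---|---|---|---|
| 5% | 1 | 5.00% | 0 |
| 5% | 2 | 5.80% | 0.80 |
| 5% | 3 | 6.56% | 1.56 |
| 10% | 1 | 10.00% | 0 |
| 10% | 2 | 11.51% | 1.51 |
| 10% | 3 | 12.90% | 2.90 |

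**5. Consequence for the comparison.** As an extreme illustration, let one group lose 20% in this way (m = 5%, k = 3) and the other lose nobody. Both curves show 5.00%, while true mortality is 6.56% and 5.00%. A difference of 1.56 points is hidden. Depending on which group loses more patients, such loss can hide or create a difference.

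**The case against.** The strongest reply is that censoring at withdrawal is standard, that withdrawal is not defined and may mean withdrawal of consent, and that rules for tracing vital status usually sit in the full protocol, the SAP or the consent form, none of which is shown. Part of this stands: withdrawal of consent to data use is a proper censoring point, and the absence of a detailed tracing procedure from an article is not a fault. What remains is that the article does state a censoring rule, makes no exception for death, and sets it beside a claim to follow all patients by identity card.

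Several stronger readings are tempting, and the article does not support them:

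- **Patients who cannot be reached are censored at last contact.** No rule for them is written. As punctuated, the last assessment is tied to experiencing a clinical event.
- **The study promises a search of the death registry.** It does not. Mortality information comes from visits and calls, and certificates confirm deaths.
- **20% are expected to be lost to mortality follow-up.** That figure is an allowance for the NIHSS outcome, which Table 1 schedules only at admission and discharge.
- **Deaths will be missed and mortality will be underestimated.** Only deaths after withdrawal are at risk of being left out, and bias requires informative withdrawal.
- **The loss can be sized with crude proportions.** With 5% mortality in 800 retained and 15% in 200 lost patients, one obtains 40/800 = 5.0% against (40 + 30)/1000 = 7.0%. This treats everyone lost as gone at the start. The planned Kaplan-Meier and Cox analyses keep each patient in the risk set until censoring.

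**Conclusion.** The concern holds in a limited form. As written, one censoring rule applies to death as to every other time-to-event outcome, and it discards deaths after withdrawal that the article's own means could capture. Taking overall mortality as one of those outcomes, the understatement is about 0.8 to 1.6 points at an assumed 5% and 1.5 to 2.9 points at an assumed 10%, when 20% leave at 1 month with 2 to 3 times the hazard. It is zero if withdrawal is unrelated to prognosis. The mortality, withdrawal proportion, timing and hazard multiples are all assumptions. Mortality is a secondary outcome and the primary NIHSS outcome is unaffected, but the correction is cheap and worth making.

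**What to change.** Reconcile Follow-Up Procedures and Statistical Analysis as follows:

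1. Separate stopping visits or calls from withdrawing consent to data use.
2. For every patient whose consent allows, obtain vital status and date of death at 6 months through the identity-card and civil-registry or hospital route.
3. Count those deaths, and censor mortality for survivors at the date of that check.
4. Censor mortality at withdrawal only when consent to data use is withdrawn.

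The cost is one vital-status check for each patient no longer in contact, consent wording that covers it, and possibly some registry delay. Recruitment began in November 2022, so for patients already enrolled the check depends on whether their consent permits it. Treatment and the primary outcome do not change.
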